### 2.1. Variables

#### 2.1.1. Independent Variable: School-Based Sexual and Reproductive Health Services

(a)Availability of services(b)Accessibility of services(c)Perceptions towards services and providers

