## 2. Methodology

The study will use an experimental research design to assess the effect of the school-based SRH services on occurrence of the adolescent pregnancy among the school girls aged 15–19 years. The Cluster Randomized Controlled Trial (CRCT) design with qualitative and quantitative components will be used as a gold standard in conducting this impact evaluation research so as to maximize comparability between the intervention and control groups, and hence give a strong evidence of a causal relationship between the intervention and the outcome [30,31,32].

The unit of randomization will be the 18 clusters (school) and 1080 individuals (girls); therefore, the cluster (school) of the eligible girls will be randomly allocated to either the intervention (9 schools) or the control (9 schools) arms of the study.

Blinding will be done to prevent systematic biases stemming from foreknowledge of group allocations among the participants and research aim outcomes as per RCT study standards [31]. Pre-determined information, such as the research hypothesis, will be concealed from the participants, data collectors, teachers and data analysts so as to prevent biases at all levels of the research. The participants will not be made aware of the research hypothesis and will be assigned any group accordingly.

In order to avoid misleading biases, the study will use the Intent To Treat (ITT) approach for analysis. Every participant allocated to a treatment group is considered to be part of the trial. ITT will be used in an attempt to avoid potential bias and identify the true effect of the intervention.

The research will use a pre-test-post-test control group approach [33]. This is where pre-intervention (baseline) measures on the prevalence of pregnancy will be conducted to allow for explicit evaluation of the pre-to-post changes.

Qualitative data will be collected through in-depth interviews of key informants in the community and discussions with groups of adolescent boys, parents, community members and school leadership. Standard guides with open-ended questions will be used for conducting the interviews and discussions. The participants of the interviews and discussions will be purposively selected based on their role in preventing adolescent pregnancy in the community.

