#### 2.1.2. Dependent Variable: Prevention of adolescent pregnancy

Primary outcomes
(a)Incidence of pregnancy(b)Sexual and Behavior change(c)Utilization of SRH services

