#### 2.8.3. Tier Three: Referrals to off-Site Public Health Facilities

The students identified in need of advanced ASRH care such as post abortion care, antenatal care and HIV treatment will be referred to primary or tertiary public health facilities for further management. Details of the reasons for referral will be recorded and a Ministry of Health (MOH) referral form filled and given to the student. The health workers at the public health facilities nearest to the school will be sensitized about the study and possible referrals to be made and a mechanism of management of the referred cases will be developed to prevent delays and stigma associated with adolescent SRH care. The district ASRH officer will take lead in this activity for ownership but also to monitor the response of health workers during the implementation.

**Follow-up:** Follow-up of the participants will be done for 12 months and data will be collected at the start of the study, after six completed months and at the end of the study after 12 months. Data on student demographics, services received and perception towards the service and provider will collected on each clinic day to assess the level of utilization and the most sought after services.

**Control Group**: The clusters in this arm will not receive any intervention from the research team. However, the participants are free to continue accessing services from the nearby facilities as has been the case prior to the study.

**Data Collection Methods:** Quantitative data will be collected using the survey method three times that is at the start of the study (0 months), six months and at the end of the study after 12 months. Qualitative data will be collected once during the 12 months of the study through interviews and discussions with the identified stakeholders. This is intended to provide subjective and relevant information to enrich the quantitative data on adolescent pregnancy in the Hoima District.

**Data Collection Tools:** Quantitative data will be collected using a self-administered questionnaire while Qualitative data will be collected using the Key Informant Interview guide and discussions using the Focus Group Discussion guides. Additional qualitative data will be collected at other SRH service delivery point to provide a snapshot on the level of utilization of services provided; this will be done using an SRH utilization register.

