## 3. Analysis

Analysis will be done using aggregate cluster-level analysis; regression analysis using individual patient data with robust standard errors; random-effects (Res) models using individual patient data; and population averaged models using individual patient data with regression coefficients estimated using generalized estimating equations (GEEs). In this study, data exploration will be done to visualize the general feature of the data then the key analysis will be by SPSS version 20 at both cluster and individual levels. Both descriptive and inferential statistics will be analyzed allowing for the association between SBSRH service and prevention of adolescent pregnancy (occurrence of pregnancy, sexual behavioral change). The intent to treat analysis will be used to analyze patients according to their random treatment assignment, which is the intended treatment, not the treatment actually received.

Descriptive summary statistics of the clusters and individuals such as frequencies, mean, medians and standard deviations will be used to describe the characteristics of the study population on sex, age, socio-economic, education level, pregnancy status and sexual behavior, among others. Summary statistics for categorical data will be displayed in form of mean, proportion, frequencies and percentages depending on the nature of the data.

To determine the association between the dependent and independent variables, a general logistic regression model will be employed and two steps will be followed. First, each variable will be entered into a binary logistic regression model. Second, variables that are found to be significant at a p-value of 0.05 will be fitted into a multiple logistic regression model to identify independent factors of influencing occurrence of adolescent pregnancy. Variables that remain significant at a p-value of 0.05 will be further analyzed using multivariate logistic regression model and variables will be identified as independent factors influencing incidence of pregnancy and behavioral change.

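### Section 2.1.1 and the logistic model in Section 3 do not name the randomised arm as the exposure, which conflicts with the commitment to analyse by random assignment

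*Protocol article*

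**What the plan says.** The heading of Section 2.1.1 gives the independent variable as the school-based SRH services. The text beneath it breaks this into three items: "a)Availability of services(b)Accessibility of services(c)Perceptions towards services and providers". Randomised allocation is not among them, nor among the intervening factors in Section 2.1.3. Section 2.1.2 lists the primary outcomes as "a)Incidence of pregnancy(b)Sexual and Behavior change(c)Utilization of SRH services".

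Section 3 links the two lists: "To determine the association between the dependent and independent variables, a general logistic regression model will be employed and two steps will be followed". The steps follow: "First, each variable will be entered into a binary logistic regression model", and then "variables that are found to be significant at a p-value of 0.05 will be fitted into a multiple logistic regression model". Variables that stay significant go into a further multivariable model and are reported as independent factors for pregnancy and behaviour change.

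Section 2 says that "ITT will be used in an attempt to avoid potential bias and identify the true effect of the intervention", and Section 3 repeats that girls will be analysed by the group to which they were randomised.

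On measurement, the follow-up paragraph in Section 2.8.3 says that data on "services received and perception towards the service and provider will collected on each clinic day to assess the level of utilization". Section 2.8.2 places the study clinics at the intervention schools.

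**The concern.** An intention-to-treat effect needs assignment as its exposure. The article's only definition of the exposure lists something else, and its most fully described outcome model is built on that definition. Taken literally, the model asks whether girls who found services available, accessible and acceptable had fewer pregnancies than girls who did not. That is an observational comparison: girls who seek out or think well of services may differ from the others in risk.

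The direction can also run the other way. Antenatal and post-abortion care are among the reasons for referral in Section 2.8.3, so a pregnancy can itself bring a girl to the service that she then rates.

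At stake is which number is read as the trial's result. If the output of this regression is reported as the effect of the package, the protection given by randomising 18 schools is lost for that estimate.

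**Working it through.** The point turns on definitions, so the check is mainly a comparison of passages.

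1. **What the trial was sized for.** Section 2.4 compares two groups at 29% and 19%: (1.96 + 0.842)² × [0.29 × 0.71 + 0.19 × 0.81] / 0.10² = 7.851 × 0.3598 / 0.01 = 282.5. The design effect is 1 + 59 × 0.01 = 1.59, and 282.5 × 1.59 = 449 per group, or 898 in total. Then 898 × 1.10 = 988, and 988 / 60 = 16.5, rounded to 17 and then to 18 clusters, giving 18 × 60 = 1080 girls. The article's figures reproduce. The contrast behind them is one group of schools against the other; availability, accessibility and perceptions play no part.

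2. **What the exposure is said to be.** Section 2.1.1 lists three items and not the arm. On-site availability is largely fixed by allocation, since the clinics are placed at intervention schools. Perceptions of services and providers belong to the individual girl and, once services run, form after randomisation.

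3. **What enters the model.** Section 3 refers to the independent variables, and Section 2.1.1 is where the article defines these. Two readings are possible:
   - Arm is not among the candidate variables. The model then contains no randomised contrast.
   - Arm is one candidate among several. It is then subject to the 0.05 screen and can be dropped. If kept, it is estimated alongside perceptions that the package may itself have changed, so its coefficient is no longer the total effect of assignment.

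   On neither reading is the intention-to-treat effect secured.

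4. **Set against the commitment.** Sections 2 and 3 promise analysis by random assignment. The cluster-level, robust-standard-error, random-effects and GEE approaches listed at the start of Section 3 could all deliver it, but no exposure term is named for any of them. The general target stated there is the association of the SBSRH service with prevention of pregnancy.

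5. **Where perceptions are measured.** The only stated collection point is the clinic day. Study clinics run at intervention schools, and control schools receive nothing from the research team. A clinic-day value therefore presupposes attendance at an intervention-school clinic. The same clinic-day record is meant to assess utilisation, which is itself a listed primary outcome. No collection point is stated for availability or accessibility.

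6. **Other sources.** A self-administered questionnaire is given at 0, 6 and 12 months, and Table 1 assigns it to all 1080 girls. Its items are not shown.

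**The case against.** The strongest reply is that the exposure is in effect the package. The heading of 2.1.1 names the services, Section 2.7 describes the arms as with and without the SBSRH package, and Section 3 names the service as the thing to be associated with prevention. On this view the three items are only dimensions of the package. Intention to treat is stated twice, and several methods suited to a cluster trial are listed. The logistic model may also be a separate risk-factor analysis, in line with the aims in Section 1 of studying barriers to services and factors associated with pregnancy.

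Much of this stands. A reader might infer that no randomised comparison is planned; the intention-to-treat statements rule that out. What the reply does not settle is the wording of the model. Section 3 does not label the logistic regression as secondary, does not name arm as its exposure and does not protect arm from the significance screen.

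A reader might also infer that perceptions are recorded exclusively at clinics, so that every control girl lacks the measure and falls out of the analysis. The documents do not support that. The text does not say that clinic days are the sole source, it ties those records to monitoring of utilisation, and the unseen questionnaire may cover the same ground. No count of missing girls can therefore be given. The clinic-day argument also reaches perceptions alone, not availability or accessibility.

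**Conclusion.** The point holds as an internal conflict that should be corrected. Section 2.1.1 and the stepwise logistic model in Section 3 describe an exposure other than randomised assignment, while Sections 2 and 3 promise analysis by assignment. As worded, the association from that model is not the randomised effect.

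This rests on reading the independent variables in Section 3 as those defined in Section 2.1.1, and on perceptions being formed once services are running. It would hold even if perceptions were measured in every girl in both arms, because they would still not be the randomised exposure. The size of any bias cannot be calculated from the document. The sample size is unaffected.

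**What to change.** - In Section 2.1.1, define the independent variable as the school's randomised allocation: SBSRH package or no package.
- In the outcome model of Section 3, name allocation as the exposure and keep it in regardless of significance.
- Describe availability, accessibility and perceptions as process measures or exploratory mediators, outside the primary effect model. If the stepwise regression is meant as a risk-factor analysis, label it so.
- If perceptions are to be compared between arms, take them from the 0-, 6- and 12-month questionnaire and say so. If the items are already there, one sentence is enough.

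The cost is a few sentences and, at most, a few added questionnaire items. No change to sample size, randomisation or visit schedule follows.

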#### 2.1.2. Dependent Variable: Prevention of adolescent pregnancy

Primary outcomes
(a)Incidence of pregnancy(b)Sexual and Behavior change(c)Utilization of SRH services

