## Abstract

Uganda has persistently had high adolescent pregnancy prevalence; 25% for the last 10 years. This protocol presents the design of a Cluster Randomized Controlled Trial (CRCT) to investigate the effectiveness of School-Based Sexual and Reproductive Health (SBSRH) interventions on prevention of pregnancy among school girls aged 15–19 years in the Hoima District, Uganda. 18 secondary schools (clusters) will be selected using cluster sampling and allocated 1:1 into control or intervention group stratified by geographical location. 1080 (60 each cluster) participants/girls aged 15–19 years will be selected using simple random sampling. The intervention group will receive tailored SRH information, in-school medical care and referral over 12 months. The control group will receive no intervention from the research team; however, they can access alternative services elsewhere if they wish. Data will be obtained at baseline, 6 months and 12 months. The outcomes are reduction in occurrence of pregnancy, utilization of SRH services and sexual behavioral change. To our knowledge, this is the first CRCT providing combined SRH interventions for prevention of adolescent pregnancy in Uganda. If effective, it could have great potential in preventing adolescent pregnancy. Trial Registration: Pan African Clinical Trial Registry (PACTR201810882140200) Registered on 16 October 2018.

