#### 2.4.2. Considerations

*π*T = Proportion of pregnant girls in group 1 approximately 29% (0.29). This is the current pregnancy prevalence in Bunyoro region (29%).

*π*C = Proportion of pregnant girls in group 2 approximately 19% (0.19). This is the expected reduction in prevalence of adolescent pregnancy after the intervention.
$$\begin{array}{lll} \mathrm{Effect}\mathrm{size} & = & 10\%[\delta \mathrm{Binary}=(\pi T-\pi C)],\mathrm{which}\mathrm{is}0.1\\ \alpha & = & 0.05(\mathrm{two}-\mathrm{sided})\\ \beta & = & 0.2\\ Z\alpha /{}_{2} & = & \mathrm{Desired}\mathrm{significance}\mathrm{level}\mathrm{at}5\%(1.96)\\ Z_{1-\beta } & = & \mathrm{Desired}\mathrm{power}\mathrm{at}80\%(0.842)\\ \mathrm{Type}\mathrm{of}\mathrm{test} & = & \mathrm{Two}-\mathrm{sided} \end{array}$$

Absolute risk reduction = 10%;

**Step One:** Formula for determining the number of subjects per group *^n^*_Individual_Binary_ for a two-sided significance level *α* and power 1 − *β*:$$\begin{array}{c} =\frac{{\left(1.96+0.842\right)}^{2}[0.29(1-0.29)+0.19(1-0.19)]}{{\left(0.29-0.19\right)}^{2}}\\ =(2.802)2[0.2059+0.1539]\\ =(7.851\times 0.3598)/0.01\\ =282.5\\ \sim 283\mathrm{individuals} \end{array}$$

**Step Two:** In order to adjust for the clustering effect, the sample size (*^n^*_Individual_Binary_) was inflated by a Design Effect (DE) to get an adjusted sample size (*^n^*_Cluster_Binary)_ [31]. Therefore, to determine the adjusted sample size per study group (*^n^*Cluster_Binary) for a Cluster Randomized Controlled Trial (cRCT), with a binary outcome, we multiply it with the Design Effect (DE):*^n^*_Cluster_Binary_ = *^n^*_Individual_Binary_ × Design effect
*^n^*_Cluster_Binary_ = *^n^*_Individual_Binary_ × [1 + (*m* − 1) *ρ*]
where *m* is the fixed cluster size and *ρ* is the Intra-cluster correlation coefficient (ICC). ICC is the ratio of the between-cluster variance to the total variance of an outcome variance and quantifies the correlation between the outcomes of any two individuals within the same cluster [31]. Since there is no previously published data/study in Uganda documenting the ICC, an ICC of 0.01 was considered because it is within the recommended inter-quantile range ICC (0.011–0.094) for previously undocumented ICC. Campbell and Walters [24] recommended a minimum cluster size of 50 subjects per cluster to cater for secondary outcomes; therefore, a fixed cluster size of 60 individuals was considered for this study.

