#### 2.8.2. Tier Two: In-School Adolescent Sexual and Reproductive Health (ASRH) Services

ASRH services will be provided at the intervention school (on-site) in an allocated room/school clinic. They will be available and accessible to all students regardless of whether they are participating in the study or not. Key services will include information, sensitive counseling, STI screening and treatment, HIV testing, contraceptives (where permitted), referral and general medical care. These will be conducted once a week by a skilled health worker recommended by the health unit in-charge at the school premises from 7:00 am to 6:00 pm. The SBHCs will be operational only during the school terms; however, their operation during the holiday will be dependent on the need and authorization from the school administration.

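### Three outcomes are named primary without ranking, but the sample size and the whole 0.05 are set for pregnancy alone, and no common two-arm measure of service utilization is stated

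*Protocol article*

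**What the plan says.** Section 2.1.2 puts three items under a single primary-outcomes label: "a)Incidence of pregnancy(b)Sexual and Behavior change(c)Utilization of SRH services". The Abstract lists the same three in another order and names no main one: "The outcomes are reduction in occurrence of pregnancy, utilization of SRH services and sexual behavioral change".

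The calculation in section 2.4.2 uses pregnancy proportions only, 0.29 and 0.19, with two-sided alpha 0.05 and 80% power. No figure for behaviour or utilization enters it. Section 3 (Analysis) mentions pregnancy and behaviour change when it describes the association to be analysed, and does not mention utilization there.

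Section 2.8 gives three sources that could bear on utilization:

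- **Clinic-day records.** "Data on student demographics, services received and perception towards the service and provider will collected on each clinic day"; their stated purpose includes assessing how much the services are used. The clinics run weekly at intervention schools (section 2.8.2), and of the services there it is said: "They will be available and accessible to all students regardless of whether they are participating in the study or not". Of the control arm: "The clusters in this arm will not receive any intervention from the research team".
- **A utilization register at other service points.** It is described as qualitative and as a snapshot.
- **A self-administered questionnaire** at 0, 6 and 12 months, which Table 1 assigns to all 1080 girls. Its items are not shown.

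**The concern.** A trial with three equal primary outcomes needs either an error rate shared among them or a rule that all must be met. A trial sized on one outcome at the full 0.05 treats that outcome as the only primary. The article does both, so a later analysis plan cannot satisfy both sections. If it tests each outcome at 0.05, the overall error exceeds 5% whenever one positive result is enough. If it divides 0.05, the stated sample size no longer gives its stated power.

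Utilization adds a problem of interpretation. The intervention places services in one arm's schools, so a difference in use largely shows that the services were delivered. With the outcomes unranked, such a difference could be reported as a primary finding alongside a null result for pregnancy, which is the stated purpose of the study.

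**Working it through.** **1. Reproduce the plan's size** (inputs from sections 2.4.2 and 2.5: proportions 0.29 and 0.19, z values 1.96 and 0.842, ICC 0.01, cluster size 60, 10% non-response)

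- Per group: (1.96 + 0.842)² × (0.29×0.71 + 0.19×0.81) / 0.10² = 7.851 × 0.3598 / 0.01 = 282.5. Stated: 282.5, about 283.
- Design effect: 1 + 59 × 0.01 = 1.59; 282.5 × 1.59 = 449. Stated: 449 per group, 898 in total.
- Non-response: 898 × 1.10 = 987.8. Stated: 988.
- Clusters: 988/60 = 16.5, taken to 17 and then 18; 18 × 60 = 1080. Stated: 1080.

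Everything reproduces, and only pregnancy enters.

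**2. Error rate if each outcome were tested at 0.05 and any one sufficed** (assumed rule)

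- Three true nulls, independent: 1 − 0.95³ = 0.143. Upper bound: 3 × 0.05 = 0.15.
- Three true nulls, equally correlated test statistics (assumed values, by simulation): about 0.125 at correlation 0.5 and 0.084 at 0.9.
- Only pregnancy and behaviour null: 1 − 0.95² = 0.0975 for those two if independent; upper bound 0.10.

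**3. Cost to pregnancy if 0.05 were split equally**

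- Alpha per outcome: 0.05/3 = 0.0167.
- Same formula at 0.0167 and 80% power: 376.7, so 377 per group; 376.7 × 1.59 = 599 per group; 1198 in total; 1198 × 1.10 = 1318; 1318/60 = 22 clusters.
- Power with the planned 18 clusters is Φ(0.10/SE − z), where SE = √(0.3598 × 1.59 / N) and N is girls per arm:

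| Girls per arm | Alpha 0.05 | Alpha 0.0167 |
|---|---|---|
| 540 (no loss) | 87% | 75% |
| 486 (10% loss) | 83% | 70% |

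These powers use the plan's own ICC and a normal approximation.

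**4. How much utilization could drive an any-one reading**

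The article gives no uptake figure, so the power of the utilization test is assumed. With no effect on pregnancy or behaviour, and independence, the chance that at least one of the three tests is positive is 1 − 0.95² × (1 − power): 0.55, 0.82 and 0.91 for utilization power of 50%, 80% and 90%.

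**5. Utilization sources side by side**

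- Clinic-day records: intervention schools only; may include girls outside the trial, because the clinics are open to all students.
- Register elsewhere: qualitative snapshot; not described as linked to enrolled girls in either arm.
- Questionnaire: both arms, same girls, three times; whether it asks about service use is not stated.

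Only the third could give a like-for-like comparison, and the article does not say that the utilization outcome comes from it.

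**The case against.** The strongest reply is that pregnancy is the main outcome in all but name. It is the heading of section 2.1.2, the first item listed, the stated purpose and the only basis of the sample size, so a null result on it would be hard to hide. Multiplicity handling and a success rule are also commonly left to an analysis plan that is not shown. Both points are fair, and the absence of a multiplicity method is not the finding. What stands is the mismatch between two things the article itself fixes: three outcomes labelled primary, and a size that spends all of 0.05 on one.

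Four stronger readings are tempting, and the article does not support them.

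- *Utilization is recorded only at intervention-school clinics.* It is not: a register at other service points and a questionnaire for all 1080 girls are also planned. Nor does the article say that the clinic-day records form the between-arm outcome; they may be meant as process data.
- *Any one positive outcome counts as success, each at 0.05.* No such rule is written. The 0.05 in section 2.4.2 belongs to the pregnancy calculation, and the 0.05 in section 3 is for carrying variables through regression models.
- *A significant utilization result is virtually certain.* No uptake, control-arm use or ICC for utilization is given. Control girls may use nearby facilities, and section 2.6 asks that schools be near a functional health centre. Only the assumed range in step 4 can be given.
- *The trial has secondary outcomes that it fails to define.* The mention of secondary outcomes in section 2.4.2 paraphrases a cited recommendation on cluster size, and is no evidence of this.

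The 14.3% also needs all three nulls to be true. If the clinics do raise utilization, the relevant bound is 10%, for the other two outcomes.

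**Conclusion.** The concern holds in this limited form. The outcome list and the sample size disagree on how many primary outcomes there are. Under an assumed any-one rule at 0.05 each, familywise error is at most 15% with three true nulls, and at most 10% if only pregnancy and behaviour are null. Under an equal split, power for pregnancy drops by 12 to 13 percentage points, to 75% or 70%. One of these follows unless pregnancy is ranked first or all three outcomes must be positive. Separately, utilization lies close to the intervention, and the article states no measure of it common to both arms. The mismatch itself rests on the text alone. The sizes rest on the plan's ICC and pregnancy proportions and on the assumptions stated with each figure.

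**What to change.** In section 2.1.2 and the Abstract, name incidence of pregnancy by 12 months as the single primary outcome, and list behaviour change and utilization as secondary. This matches the outcome used in section 2.4.2, leaves 898, 988 and 1080 unchanged, and removes the multiplicity among primary outcomes. Testing the three in fixed order with pregnancy first would also keep the size. Keeping three equal primaries with 0.05 split would need about 22 clusters of 60.

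State that utilization is compared between arms only from the same 6- and 12-month questionnaire in enrolled girls, covering any SRH service from any source, and that clinic-day records are reported as process data for the intervention arm.

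The cost is a change of wording and of outcome labels. If the questionnaire does not already ask about service use from any source, an item must be added; the survey rounds themselves are already planned. The downside is that behaviour change and utilization can no longer be claimed as primary successes.
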